## Abstract

**Background:**

Randomized studies have demonstrated that high-volume hemodiafiltration results in reduced mortality compared to conventional hemodialysis treatment. However, eligibility criteria in these trials may limit generalizability to routine clinical practice. Some of these trials reported a limited number of events, underscoring the need to further evaluate the effect of hemodiafiltration on mortality. We will conduct a target trial emulation study using data from routine clinical practice. The primary aim of this study is to evaluate whether high-volume hemodiafiltration reduces all-cause mortality. The secondary aim is to assess cause-specific mortality. Other aims include assessing all-cause and cause-specific hospitalizations, as well as cumulative length of hospital stay and the dose–response relationship between convection volume in hemodiafiltration and the outcomes.

**Methods:**

Data will be obtained from the second version of ApolloDialDb (Apollo), an anonymized dialysis dataset capturing over 1000 variables from patients from all over the world. For this study, we will include adult patients from European countries with kidney failure who initiated with at least one treatment of high-flux hemodialysis or hemodiafiltration between 01 January 2018 and 30 June 2024, and who were prescribed a thrice-weekly dialysis schedule at the start. Patients starting with home dialysis will be excluded. We will use a target trial emulation approach with a clone-censor-weight design and marginal structural models, controlling for selection bias, survivor bias, and competing risk bias. Sub-analyses will be performed to investigate the effect of high-volume hemodiafiltration (≥ 23 L of convection volume). Inverse probability weighting will be applied to adjust for predefined confounders including sociodemographic, clinical, and anthropometric factors, as well as comorbidities to achieve balance between treatment groups.

**Discussion:**

In addition to randomized studies, prior large observational studies have indicated a survival benefit for hemodiafiltration, as well as a possible reduction of hospitalizations. The target trial emulation study outlined in this protocol will expand this knowledge and provide generalizable insights on the effects of hemodiafiltration on outcomes by using real-world data representative of routine clinical practice while appropriately addressing sources of bias.

**Graphical abstract:**

**Figure Figa:**
[figure not shown]

**Supplementary Information:**

The online version contains supplementary material available at https://doi.org/10.1186/s12882-026-05315-z.

## Background

The CONVINCE randomized controlled trial (RCT) demonstrated that high-volume hemodiafiltration (HDF) improved survival compared with standard high-flux hemodialysis (HD) [1]. More recently, an individual patient data meta-analysis that combined CONVINCE with four previous randomized trials showed a further reduction in mortality risk with increasing convection volumes [2]. These effects were consistent across patient and treatment characteristics.

However, eligibility criteria in these trials may limit generalizability to routine clinical practice. In CONVINCE, patients were enrolled only if a convection volume of at least 23 L per session was considered achievable. The other trials applied several strict inclusion and exclusion criteria, which excluded people with an active infection or systemic disease, malnutrition, uncontrolled anemia, or those taking any immunosuppressive therapy [3–5]. Consequently, the findings may not fully represent outcomes in the broader dialysis population. Several observational studies have also indicated a survival benefit and a reduction of hospitalizations with HDF [6–11]. However, observational studies are often confounded by several forms of bias (immortal time or survival bias, prevalent user or selection bias) because of their design.

Target trial emulation addresses this gap by applying a RCT framework to observational data, thereby enabling causal inference within observational data captured in and representative of routine clinical practice [12]. The primary aim of this predefined study protocol is to evaluate whether high-volume HDF reduces all-cause mortality compared to HD in routine clinical practice, and the secondary aim is to assess cause-specific mortality. Other aims include assessing all-cause and cause-specific hospitalizations, as well as cumulative length of hospital stay and the dose–response relationship between HDF convection volume and outcomes.

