	**Treatment strategies**	
	1. Initiate HDF within the first 90 days after dialysis initiation (grace period) and continue HDF throughout the grace period receiving at least three HDF treatments every two weeks. 2. Initiate HD within the first 90 days after dialysis initiation (grace period) and continue HD throughout the grace period receiving more than three HD treatments every two weeks.	Same as target trial

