### Treatment strategies

We will compare the initiation of HDF with the initiation of high-flux HD. Aligning study eligibility, treatment assignment, and the start of follow-up is essential to prevent immortal time bias. However, this alignment is challenging because many patients switch between HD and HDF over time, and patients often initiate incenter dialysis with HD and subsequently transition to HDF at a later stage, calling for an approach that can accommodate practice patterns and dynamic treatment strategies.

Therefore, we will implement two different methods of analysis. First, we will use the clone-censor weight (CCW) approach. This approach begins with the duplication each individual (creation of “clones”) at the start of follow-up (first dialysis initiation) and each clone will be assigned to either the HDF strategy or the HD strategy.

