**HDF strategy:**

Initiate HDF within the first 90 days after dialysis initiation (grace period).Continue HDF throughout the grace period (receiving at least three HDF treatments every two weeks).

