**HD strategy:**

Initiate HD within the first 90 days after dialysis initiation (grace period).Continue HD throughout the grace period (receiving more than three HD treatments every two weeks).

The 90-day grace period was selected based on the expectation that patients who transition to HDF generally do so within the first three months after dialysis initiation. Similarly, the definition of treatment continuation as receiving at least three HDF treatments every two weeks was based on clinical practice patterns. After assignment, clones are followed and censored in case they deviate from the assigned treatment strategy during the grace period of 90 days. In addition to this approach, we will use a Marginal Structural Model (MSM) to estimate the effect of sustained treatment with HDF versus sustained treatment with HD. For this model, follow-up will start at dialysis initiation, and treatment will be included as a time-varying covariate throughout the entire follow-up period.

Lastly, we will conduct additional analyses for both the CCW approach and MSM in which we will evaluate consistent treatment strategies, but with HDF redefined as achievement of high-volume HDF (≥ 23 L of convection volume). For the CCW approach, we will calculate the mean delivered convection volume for every two-week period within the grace period. For MSM, we will calculate the mean delivered convection volume for every six months.

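### The primary aim concerns high-volume HDF, but the lead analysis compares HDF at any convection volume with HD

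*Protocol article*

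**What the plan says.** The primary aim appears twice, each time for high-volume HDF. The Abstract (Background) has "The primary aim of this study is to evaluate whether high-volume hemodiafiltration reduces all-cause mortality". The main Background section repeats it and adds the comparator: "The primary aim of this predefined study protocol is to evaluate whether high-volume HDF reduces all-cause mortality compared to HD in routine clinical practice".

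The strategies are worded differently. The Treatment strategies section opens with "We will compare the initiation of HDF with the initiation of high-flux HD". In Table 1, a patient in the HDF arm must start HDF within the 90-day grace period and "continue HDF throughout the grace period receiving at least three HDF treatments every two weeks". The HDF strategy paragraph in the text sets the same two conditions. Neither place mentions convection volume.

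High volume comes in at a lower rank. The Abstract (Methods) says "Sub-analyses will be performed to investigate the effect of high-volume hemodiafiltration", with 23 L as the threshold. The text under HD strategy comes to it last: "we will conduct additional analyses for both the CCW approach and MSM in which we will evaluate consistent treatment strategies, but with HDF redefined" to mean reaching at least 23 L. Delivered volume is averaged over two-week periods for the clone-censor-weight (CCW) approach and over six-month periods for the marginal structural model (MSM).

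**The concern.** The aim tells the reader which question the study will answer. The target-trial table tells the reader which intervention is emulated. Here the two differ in convection volume, an attribute that the article itself treats as important. Its Background cites an individual patient data meta-analysis in which mortality risk fell further as convection volume rose. It also notes that a cited randomized trial enrolled only patients for whom 23 L per session was thought achievable. The present study has no such entry condition, so its HDF arm may mix volumes.

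HDF at whatever volume is delivered and HDF at 23 L or more are therefore different interventions and may have different effects. If the lead result is read against the stated aim, an error is possible in either direction. A weak any-volume result could be taken as evidence against high-volume HDF, and a favourable one could be taken as confirmation of it.

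**Working it through.** The article states no sample size, effect size or event count that bears on this point, so there is no figure to reproduce. The check is to compare the contrast at each place where the article fixes one.

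1. **Aim** (Abstract, Background; main Background section): high-volume HDF versus HD, all-cause mortality.
2. **Table 1, treatment strategies**: HDF defined by initiation within 90 days and a minimum session frequency. No volume.
3. **Treatment strategies section and HDF strategy paragraph**: the same definition. No volume.
4. **MSM contrast** (text under HD strategy): sustained HDF against sustained HD. No volume.
5. **Interpretation and estimands**: CCW compares starting HDF within 90 days with not starting it; the MSM compares sustained HDF with sustained HD. No volume in either.
6. **Sub-analyses and additional analyses** (Abstract, Methods; text under HD strategy): HDF at 23 L or more versus HD, under both CCW and MSM. This is the only planned contrast that matches item 1.
7. **Dose-response** (Table 1, other outcomes; Outcomes section): convection volume as a continuous variable among patients receiving HDF. It has no HD arm, so it cannot stand in for item 6.
8. **Discussion**: the contribution is described as the effectiveness of HDF compared with high-flux HD, again without a volume.

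Which analysis leads? None carries the label primary, so its rank has to be read from the text. CCW is introduced first, the MSM is added to it, and high volume comes last. Table 1, which the article presents as the protocol of the target trial, contains only the any-volume strategies. The additional analyses are described as redefining HDF, which confirms that the main definition is not high-volume. The lead contrast is thus CCW with HDF at any volume (items 2, 3 and 5), and it differs from item 1.

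How large is the gap? It depends on the share of HDF that reaches 23 L and on the effect of HDF below that threshold. If all HDF reached 23 L, the two contrasts would coincide. Otherwise they coincide only if HDF below 23 L has the same effect as HDF above it. The article gives neither quantity.

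**The case against.** The strongest reply is that the high-volume question is not neglected. A comparison with HD is committed to under both methods, with a threshold and averaging windows fixed in advance. That is correct, and it limits the point: a matching analysis exists but is ranked below one that does not match. A reader might infer that the study never tests its primary aim; the article does not support that.

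A second reply is that calling the any-volume analysis primary is itself an inference, and that a condensed article may leave the formal hierarchy to an analysis plan that is not shown. The inference is acknowledged above. The point does not rest on a missing hierarchy, however. It rests on two statements in the article, the aim and the target-trial table, that disagree about the intervention.

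A reader might also go further and count CCW and MSM, each at any volume and at high volume, as four rival primary contrasts from which a headline could be picked once results are known. That goes too far. The order of presentation and Table 1 already point to one lead contrast. The conflict is between that contrast and the aim.

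**Conclusion.** The point stands as an inconsistency between the stated primary aim and the lead analysis. Following the plan as written would set an any-volume estimate against a high-volume aim, and nothing else in the article reconciles the two. The conclusion rests on reading Table 1, the order of the text and the additional status of the 23 L analysis as showing which contrast leads.

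The size of the consequence is unknown. A reader might try to put a dilution factor on the any-volume hazard ratio by assuming a benefit at 23 L and none below it. The article supplies no hazard ratio for either range and no share of high-volume treatment. The gradient that it cites also does not imply a null effect below a cut-off. No figure is therefore offered.

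**What to change.** Before outcome analysis, make the primary aim and the lead contrast the same and name that contrast as primary. Two routes achieve this, and the choice is the sponsor's.

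- **(a)** Restate the primary aim and the planned conclusion as HDF at any delivered volume versus high-flux HD, and list the high-volume contrast as a named secondary analysis. The cost is that the primary conclusion no longer speaks directly to high-volume HDF. It would concern a broader exposure.
- **(b)** Keep the high-volume aim, place the protocol's own 23 L strategy in Table 1 and in the estimands as the primary HDF strategy, and make any-volume HDF secondary. The cost is likely to be some precision. The volume condition adds to the existing adherence rules, so every HDF clone censored under the any-volume rule would still be censored, and those averaging below 23 L would be censored as well.

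Either route needs edits to the Abstract, Background, Table 1 and the estimand section so that they agree. Both analyses are already planned, so no new data or models are required.

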## Methods

### Datasource

Data will be obtained from the second version of ApolloDialDb (Apollo), an anonymized global dialysis dataset across 41 countries. This database contains longitudinal data on dialysis treatments from a global kidney provider network (Fresenius Medical Care, Bad Homburg, DE) [13, 14]. This second version of Apollo contains data from 113,415 patients on dialysis from Europe [14]. This includes demographic and laboratory data, dialysis specific data as well as medication use, and clinical diagnoses. Data from dialysis sessions or mortality occurring in the hospital during a hospitalization throughout the dialysis course has been registered from the respective hospital and is included in the database.

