	**Analysis plan**	
	• Intention-to-treat analysis, see Follow-up for censoring.	• Per protocol effect, see Follow-up for censoring. • Analysis is conducted in expanded data set that includes two clones for each eligible patient (one for each treatment strategy). IPCW is performed, both for informative and artificial censoring within the grace period, and for informative censoring after the grace period.

*Although this may theoretically lead to some level of immortal time bias, excluding everyone who does not have any data at day one of dialysis initiation will lead to selection bias (due to missingness). As the database for this study contains treatment related data in an outpatient setting, hospitalization at the start could be the reason for missing data in the first period

♠ To protect patient privacy, only the calendar quarter of dialysis initiation is available. We will therefore assign the midpoint of the quarter as the initiation date, as this approach minimizes misclassification. As a result, the maximum follow-up period will be 4 years and 9 months

HDF, hemodiafiltration; HD, hemodialysis; ICD-10, International Classification of Diseases; IPCW, inverse probability of censoring weighting

Inclusion criteria for this study will be:

Patients with age ≥ 18 years old at baseline;Patients with kidney failure who initiate dialysis and receive at least one high-flux HD or HDF treatment between 1 January 2018 and 30 June of 2024;Treatment occurs in a European country where both HDF and HD are available and where patients in the dataset receive both modalities each calendar year, ensuring representation of both treatments within each country;Patients prescribed thrice-weekly dialysis at the start.

Exclusion criteria will be:

Patients starting with dialysis at home;Patients who do not have the first treatment-related data available within 14 days after dialysis initiation.*.

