*Because this database captures outpatient treatment only, data at treatment initiation may be missing for patients who were at another dialysis provider or who were hospitalized at that time. Excluding these patients could therefore introduce selection bias. Including patients with available data within the first 14 days may introduce a degree of immortal time bias; however, we believe for 14 days this will be limited. We will perform subgroup analyses of patients who have first treatment data at dialysis initiation compared to patients of whom first data is available within 14 days but not at the first initiation.

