Second, the Apollo database only captures outpatient dialysis treatments from a single dialysis provider. Although it includes a large number of patients from different European countries, the focus on Europe and the use of data from a single provider may limit generalizability to other regions and healthcare settings. Furthermore, treatment-related data at dialysis initiation are unavailable for patients hospitalized during the first period. To reduce the potential for selection bias, patients with available treatment data within the first 14 days after dialysis initiation will be included. This approach may introduce a limited degree of immortal time bias, however, we considered this risk to be outweighed by the selection bias that could arise from systematically excluding patients requiring hospitalization shortly after dialysis initiation. We will perform subgroup analyses to evaluate the results in this group who does not have available data at the first treatment.

Finally, despite extensive adjustment strategies and the use of advanced causal inference methods, residual confounding cannot be fully eliminated, as is inherent to observational research. Some variables were not registered systematically such as ambulatory blood pressure measurements, functional status or cardiac function as measured on echocardiogram. Therefore, we could not include these into the analyses. Nevertheless, by explicitly emulating a target trial and applying causal analytic methods to a large real-world dataset, this study seeks to provide clinically relevant and more generalizable evidence regarding the effectiveness of HDF.

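### The article contradicts itself on whether dialysis sessions given in hospital are in the data, and under either reading the two-weekly session count can turn an admission into censoring or an apparent modality switch

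*Protocol article*

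**What the plan says.** On the content of the database, the protocol article makes these statements:

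- Datasource: "Data from dialysis sessions or mortality occurring in the hospital during a hospitalization throughout the dialysis course has been registered from the respective hospital". The sentence goes on to say that these data are in the database.
- Footnote to the exclusion criteria (Study design and patient selection): "Because this database captures outpatient treatment only".
- Footnote to Table 1: "As the database for this study contains treatment related data in an outpatient setting, hospitalization at the start could be the reason for missing data".
- Discussion, limitations: "the Apollo database only captures outpatient dialysis treatments from a single dialysis provider".

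On how exposure is built from sessions:

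- HDF strategy: "Continue HDF throughout the grace period (receiving at least three HDF treatments every two weeks".
- HD strategy: "Continue HD throughout the grace period (receiving more than three HD treatments every two weeks".
- CCW approach: adherence is checked every two weeks, and a death counts only for a clone that has not yet been censored.
- Interpretation and estimands: adherence matters only inside the 90-day grace period; later changes of modality are ignored.
- Marginal structural model (MSM): "treatment will be included as a time-varying covariate throughout the entire follow-up period", with treatment and censoring weights estimated every six months.

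The article does not say how sessions given in hospital, or absent because of a hospital stay, enter the two-weekly count or the MSM treatment variable.

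**The concern.** Statements about which sessions exist in the data are not background detail here, because sessions define exposure, adherence and censoring. A patient admitted during the grace period is more likely to die than one who is not. If the admission itself changes the recorded session counts, it can remove that patient's clone from an arm, or make the patient look like a switcher, for a reason unrelated to any choice of modality. Deaths that follow are then lost to one arm or counted in the other.

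The two readings lead to different errors. If inpatient sessions are recorded, the risk is a false switch. If they are not, the risk is that absence from the outpatient unit is read as non-adherence. A reader cannot tell from the article which of these to look for, and the analyst cannot tell which to guard against.

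**Working it through.** There is no figure in the plan to reproduce. The check applies the stated session rules to a two-week window under each reading.

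Inputs:

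- Thrice-weekly prescription at the start (inclusion criteria): 2 × 3 = 6 sessions per window.
- HDF rule (Treatment strategies): HDF sessions ≥ 3.
- HD rule (Treatment strategies): HD sessions > 3, so at least 4.
- *h* = number of the six sessions that fall in hospital, leaving 6 − *h* outpatient sessions.
- Assumption for the first reading only: the hospital gives HD. The article does not state inpatient modality.

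| *h* | Outpatient sessions | Inpatient HD recorded, HDF patient: HDF rule / HD rule | Inpatient not recorded, HDF patient: HDF rule | Inpatient not recorded, HD patient: HD rule |
|---|---|---|---|---|
| 0 to 2 | 6 to 4 | met / not met | met | met |
| 3 | 3 | met (3 ≥ 3) / not met (3 is not > 3) | met (3 ≥ 3) | fails (3 is not > 3) |
| 4 | 2 | fails (2 < 3) / met (4 > 3) | fails (2 < 3) | fails (2 is not > 3) |
| 5 or 6 | 1 or 0 | fails / met | fails | fails |

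**Inpatient sessions recorded.** From *h* = 4 the HDF patient's window reads as HD: the HDF clone is censored and the HD rule is satisfied. A death after that window no longer counts for HDF. The mirror case, an outpatient HD patient given HDF in hospital, flips at *h* = 3 (HD 3, not > 3; HDF 3 ≥ 3).

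**Inpatient sessions not recorded.** No assumption about inpatient modality is needed. Three missing sessions, about one week at three per week, are enough to censor an HD patient's HD clone. An HDF patient's HDF clone survives three and fails at four. The thresholds differ by arm because one rule is at least three and the other is more than three.

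**Reach in CCW.** Adherence is assessed for 90 days, or 90 / 14 ≈ 6.4 windows. Nothing after day 90 is affected.

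**Reach in the MSM.** A six-month interval holds about 26 × 3 = 78 sessions. Four inpatient sessions are 4 / 78 ≈ 5%. A majority rule would need 40 of 78 to change class, so a short admission would not move it; a rule based on the last session could be moved by one. The article does not state which rule applies.

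**The case against.** The strongest reply is that the statements concern different times: the outpatient-only remarks explain gaps at the start of dialysis, while Datasource describes later admissions. The footnote does apply its premise to initiation ("Because this database captures outpatient treatment only, data at treatment initiation may be missing"), but that premise, and the sentence in the Discussion, describe the database as a whole. Even if the reply is accepted, inpatient sessions are then in the data after initiation, which is the first reading above.

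A second reply is that coding of sessions during admissions is detail that an article may leave to a fuller document. That would hold if the article were merely silent. Here it gives conflicting descriptions of the source data and fixes numerical counts that act on them.

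Other parts of the opposing case stand:

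- A reader might infer that capture of in-hospital deaths, and so of the primary outcome, is in doubt. The article does not support that. The outpatient-only statements limit treatment data, not deaths, and Datasource already names the hospital as the source of in-hospital mortality.
- A reader might infer a bias in favour of HDF, with dying HDF patients moved to HD. That requires hospitals to give mainly HD, which is not documented, and ignores the mirror case.
- The censoring weights, and in the MSM the treatment weights, may offset part of the problem if they include markers of acute illness. The covariates are in Fig. 1, which was not available, so their absence cannot be presumed.
- The CCW approach lets a death in the grace period count in both arms when only one modality was received. If this overrides the two-weekly count, it protects some deaths when inpatient sessions are unrecorded. The text does not say which takes precedence, and the provision would not literally cover a patient with a recorded inpatient session in the other modality.

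**Conclusion.** The contradiction is certain and lies in the current text. Its consequence for CCW follows from the stated counts: four of six inpatient sessions given as HD (assumed) turn an HDF window into an HD window, or, if inpatient sessions are unrecorded, three missing sessions censor an HD patient's HD clone and four an HDF patient's HDF clone. This rests on a literal application of the counts to a six-session window. It is confined to the first 90 days in CCW and depends on an unstated interval rule in the MSM.

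The direction and size of any bias cannot be determined, because neither inpatient modality nor the frequency of admissions in the grace period is given. The point is a conflict that leaves the exposure definition open to error, not a demonstrated bias, and it does not extend to the capture of deaths.

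**What to change.** 1. Check session records against admission dates to establish whether inpatient sessions are present, then make Datasource, the Table 1 footnote, the exclusion-criteria footnote and the Discussion agree.
2. In both analyses, define exposure and adherence from outpatient sessions. During an admission, carry the last outpatient modality forward, so that inpatient or missing sessions do not by themselves count as non-adherence or as a switch. Recognise a change once the new modality is delivered after discharge.

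The cost is wording in four places and one coding rule. No new data should be needed: hospitalizations and length of stay are already outcomes, provided that admissions and sessions can be placed on the same time scale. The downside is that a true switch made during an admission is recognised only after discharge.
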